### Reliability

Reliability of the WORC is tested by comparing the results at T0 with T1. T1 is planned 2-3 weeks after T0, because we expect that the symptoms do not change between these two moments and the time span is large enough to forget initial responses to the questions. In order to signal change in severity of the symptoms, at both moments patients are asked to rate their shoulder hindrance. To determine test-retest reliability, intraclass correlation coefficients (ICC) are used.

### Validity

Criterion validity is measured by comparing WORC with a general quality of life questionnaire (SF-36) and a commonly used clinical shoulder score (Constant Score) both at T0 and T1. Bland Altman plots will be used to estimate 95% boundaries of concurrence.

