The WORC is used in research [17] and has already been translated into German [18], Iranian [19], Norwegian [20], Portuguese [21] and Turkish [22]. A Dutch translation of the WORC will be used in our clinic. This translation was performed by linguistic validation, which is not a literal translation but a stepwise process to produce a conceptually equivalent of the original questionnaire[23]. The process was controlled with final approval by one of the authors of WORC[15]. In this study the Dutch version of the WORC is validated.

As far as we know the WORC has not been tested on a group of patients with arthroscopic rotator cuff repair. In the WORC article by Kirkley et al[15]. validity as an evaluative tool was tested in a group of 50 patients with disorders of the rotator cuff (DRC) who reported that their symptoms had changed. Forty-six were treated with injection therapy and only four underwent subacromial decompression[15]. In order to use the test in those who underwent arthroscopic rotator cuff repair, the WORC should be tested in a group of patients treated with this type of repair.

The aim of this study is to investigate reliability, validity and responsiveness of WORC in patients undergoing arthroscopic rotator cuff repair. Because there is no gold standard we are aiming to assess construct validity, i.e. the extent to which WORC scores relate to SF-36 and Constant Scores. More experiences with the disease specificity of the use of the WORC are needed, since this instrument is designed for use in patients with DRC only.

Therefore, three groups of patients are chosen in which the WORC will be tested. These groups contain patients with respectively:

1. Arthroscopic rotator cuff repair;

2. DRC without rupture;

3. Shoulder instability.

We hypothesize that the Dutch translation of WORC:

• has a high reliability (ICC > 0,9) in all 3 groups;

• has a high validity compared to SF-36 and Constant Scores in groups 1 and 2. We expect correlations on the SF-36 and Constant Score to lie around 0.6 and an inverse correlation between Constant Score and SF-36 versus WORC around -0.5[22]; The relation is expected to be negative due to the construction of WORC, in which a high score corresponds to a disabled shoulder, while a high Constant Score and SF-36 match with little disability.

• has a high responsiveness in groups 1 and 2;

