By now, arthroscopic rotator cuff repair is a commonly accepted treatment. We also want to use the WORC to measure the results of our arthroscopic rotator cuff repairs. In patients with DRC the WORC is an appropriate measurement tool[15]. We will investigate whether this also accounts in patients with arthroscopic rotator cuff repair. To do so we investigate a group of patients with arthroscopic rotator cuff repair. A second group is used existing of patients with DRC analogical to the group used by the developers of the WORC. And in order to investigate specificity within the shoulder pathologies it is tested on a group of patients with a different type of shoulder complain, instability.

Reliability is tested by comparing T1 and T0 in the three groups. Concerning validity we are aiming to assess construct validity, i.e. the extent to which WORC Scores relate to SF-36 and Constant Scores. Construct validity can be assessed by comparing the convergent/discriminant validity across instruments and patient groups ('known-groups validation', hence the three patient groups). It should be noted that the study will not truly be able to assess disease specificity of the WORC because the three patient groups differ not only with respect to diagnosis, but also with respect to treatment modality. The Constant Score was elected to correlate with, because it is a clinical score which is commonly used and widely accepted in Europe[13]. Responsiveness is tested by comparing T2 and T0.

The name of the WORC implies specificity to rotator cuff disease, although it has been developed to assess quality of life regarding DRC, and not as a discriminative tool[15]. Therefore, the results of the WORC in group 1 and 2 are compared with a third group consisting of patients with instability to investigate specificity.

The method of patient assignment could be a subject of criticism. Patients were assigned to a certain group based on a combination of clinical symptoms and findings on MRI, Ultrasound or X-ray, because the clinical tests for DRC and shoulder instability lack high accuracy[30,54-58]. However, this was then confirmed during arthroscopy.

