## Appendix

### Description of WORC and item selection

The Western Ontario Rotator Cuff Index (WORC) [15] is designed for patients with disorders of the rotator cuff[15]. It is an HRQL-questionnaire that has 21 items representing 5 domains, each with a visual analogue scale-type response option. The 5 domains are (1) physical symptoms, (2) sports and recreation, (3) work, (4) social function, and (5) emotions. WORC items are scored on a 100-point scale (ranging from 0-100). The most symptomatic score is 2100, and the best, or asymptomatic, score is 0. To present this in a more clinically meaningful format, the score can be reported as a percentage of normal by subtracting the total from 2100, dividing by 2100, and multiplying by 100. Total final WORC scores can, therefore, vary from 0%, the lowest functional status level, to 100%, the highest functional status level [59].

Items for the WORC were derived from published health status scales, functional measures of the shoulder, discussions with healthcare professionals, and interviews with 30 patients from a registry of 150 with rotator cuff pathology. Both professionals and patients were asked to identify ways in which the shoulder condition affected quality of life in general and the 5 domains in particular. The 30 patients interviewed included males and females, aged 30-76, with different degrees of rotator cuff pathology from tendinitis to massive tears.

An original list of 321 items was reduced to 76 by the investigators eliminating duplicated, incomprehensible or ambiguous items. A random selection of 100 patients from the same registry were then asked to indicate whether they experienced each of the items, and to rate the importance of the symptom/disability to their overall shoulder functioning. A frequency importance product was calculated for each item and the 50 items with the highest values were correlated with each other. For every pair of items with coefficients greater than 0.6, one of the items was eliminated, resulting in the final 21 questions. It is not clear whether this criterion applied to items across domains because the only example provided included 3 items from the same domain[60].

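### The Validity section names only Bland-Altman limits, labelled criterion validity, for a construct-validity hypothesis that the protocol states as correlations

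*Protocol article*

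**What the plan says.** The Validity section has two sentences. The first gives the label and the comparators, at both T0 and T1: "Criterion validity is measured by comparing WORC with a general quality of life questionnaire (SF-36) and a commonly used clinical shoulder score (Constant Score". The second gives the only statistic named there: "Bland Altman plots will be used to estimate 95% boundaries of concurrence".

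The Background describes the target differently: "Because there is no gold standard we are aiming to assess construct validity". The Discussion repeats this: "Concerning validity we are aiming to assess construct validity, i.e. the extent to which WORC Scores relate to SF-36 and Constant Scores".

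The Background states the validity hypothesis, for groups 1 and 2, as correlations: a value around 0.6 (the sentence leaves unclear which pair of scores is meant) and an "inverse correlation between Constant Score and SF-36 versus WORC around -0.5". It explains the minus sign by the construction of the WORC, "in which a high score corresponds to a disabled shoulder". The appendix on the WORC gives the raw total as 0 (best) to 2100 (worst) and allows conversion to a percentage: "Total final WORC scores can, therefore, vary from 0%, the lowest functional status level, to 100%, the highest functional status level". The Validity section does not say which form enters the plots.

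**The concern.** There are two mismatches, and both are in what the text states.

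- **Label.** Criterion validity needs a criterion. The Background says none exists and sets construct validity as the aim.
- **Method.** Limits of agreement ask whether two measurements of the same quantity, in the same units, can replace each other. Here a disease-specific quality-of-life index is set against a generic quality-of-life questionnaire and a score that the appendix describes as a measure of shoulder function alone. The protocol's own expectation of a correlation near 0.5 in size shows that it does not expect them to be interchangeable.

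Validity is one of the three stated aims, beside reliability and responsiveness. If the section is followed as written, its output will be a set of limits that bear on no stated hypothesis, while the correlation that the Background predicts has no analysis named for it in that section.

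**Working it through.** The protocol gives no limit of agreement and no acceptance bound for this analysis, so there is no figure of its own to reproduce. The check asks what the named statistic would show if the hypothesis were exactly true.

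**Inputs**
- Expected correlation of the WORC with the comparators: about -0.5 with the raw WORC (Background), hence +0.5 once directions are aligned.
- WORC range: 0-2100 raw, or 0-100% reversed (appendix).
- Group size: 30 (Patient assignment).
- Assumed, because the document gives none: 0-100 comparator scales and SDs of 15, 20 and 25 points.

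**Formula.** Half-width of the limits = 1.96 × √(s1² + s2² − 2·r·s1·s2). With equal SDs s this is 1.96 × s × √(2(1 − r)).

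**Aligned 0-100 scales, r = 0.5.** Here √(2 × 0.5) = 1, so the half-width is 1.96 × s:
- s = 15: ±29.4
- s = 20: ±39.2
- s = 25: ±49.0

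**Aligned, s = 20, higher correlations**
- r = 0.6: 1.96 × 20 × √0.8 = ±35.1
- r = 0.7: 1.96 × 20 × √0.6 = ±30.4

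So r = 0.5 with SD 15 (±29.4) and r = 0.7 with SD 20 (±30.4) give almost the same limits. The limits do not identify the correlation.

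**If the scales were not aligned (conditional; the text does not say so)**
- Both on 0-100, opposite directions, s = 20, r = -0.5: 1.96 × √1200 = ±67.9.
- Raw WORC with SD 420 (20% of 2100) against SD 20, r = -0.5: 1.96 × √(176,400 + 400 + 8,400) = 1.96 × 430.3, about ±843.

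**Trend of difference against mean.** The correlation of difference with mean is (s1² − s2²) / (SD of difference × SD of sum). With equal SDs it is 0. With SDs of 20 and 10 on aligned scales at r = 0.5 it is 0.65, from scaling alone. In the raw case it is 176,000 / (430.3 × 410.4), about 0.997, so that plot would show little except the WORC score itself.

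**What a correlation would deliver.** Fisher z 95% interval for r = 0.5, n = 30: 0.549 ± 1.96/√27 = 0.549 ± 0.377, which transforms back to 0.17 to 0.73. For groups 1 and 2 pooled (n = 60) it is 0.28 to 0.67.

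**The case against.** The strongest reply is that the protocol does have a route to construct validity. The Background states correlation hypotheses, the Discussion names convergent/discriminant and known-groups validation, and the Responsiveness section plans a comparison of WORC scores across the three groups. A condensed article may also leave the choice of coefficient and its interval to a fuller plan. Much of this stands. A reader might infer that the protocol cannot address validity at all, or that its hypotheses have no planned test anywhere; the documents do not support that. What remains is not an omission, because the article itself fixes an unsuitable statistic and a label that its own Background contradicts.

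Other stronger readings also fail:
- **That the WORC would be declared invalid because the limits are wide.** The text sets no acceptance limit and no decision rule.
- **That a trend against the mean must appear.** With equal SDs it does not; it needs unequal SDs or raw scores.
- **That limits of ±68 or ±843 are to be expected.** These need unaligned or raw WORC scores, and nothing says those are plotted. The Background shows that the authors know the direction is reversed, and the appendix gives the conversion.
- **That the negative sign is an error.** It is right for the raw score. Converting to the percentage only changes the sign and leaves the size of r as it was, so the need is simply to say which form is used.

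A defence that the percentage score solves the problem does not succeed either: it aligns range and direction, but the constructs still differ, and the limits remain about ±39 at SD 20.

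**Conclusion.** The point holds for the Validity section as written. Its label conflicts with the Background and the Discussion, and the one statistic it names does not match the correlation hypothesis. This follows from the text and rests on no assumed figure. The sizes are illustrative: about ±29 to ±49 points at the predicted |r| = 0.5 on aligned 0-100 scales, assuming equal SDs of 15 to 25. They would be wider still, or show a trend, only if raw or unaligned scores were plotted. The known-groups comparison is untouched. No data are lost, since all three instruments are collected at T0 and T1 and the correlations can be computed.

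**What to change.** In the Validity section:

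1. Replace criterion validity by construct (convergent) validity, in line with the Background and the Discussion.
2. Replace the Bland-Altman comparison with the SF-36 and the Constant Score by Pearson or Spearman correlations per group with 95% confidence intervals, reported against the expected values. The interval matters because 30 patients leave r = 0.5 imprecise.
3. State whether the raw or the percentage WORC is used, and give the expected sign to match: negative for raw, positive for percentage.

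Optionally, use Bland-Altman for the WORC at T0 against T1, alongside the planned ICC. There the instrument and the units are the same, so the limits have a meaning.

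The cost is wording only: no new data, visits or patients.

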### Responsiveness

Responsiveness, or the ability of an instrument to detect clinically important change, will be determined by calculating the standardized response means and effect sizes on T0 and T2 scores on WORC, SF-36 and Constant scores for the subgroups. The magnitude of the standardized response mean (mean change in score from T0 to follow-up (T2)/standard deviation of change in score) and the effect sizes (mean change in score from T0 to follow-up (T2)/standard deviation of T0 score) will be interpreted using the Cohen standard of greater than 0.20 for small effects, greater than 0.50 for moderate effects, and greater than 0.80 for large effects.

Finally, a comparison of WORC scores between the three distinct groups is made, to see whether WORC scores can differentiate between them. WORC scores will be compared with SF-36 to investigate whether the noted differences correlate with notable clinical differences and can be expressed as MCID's (minimal clinical important differences)[33].

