#### Patient routine

Prior to the first visit to the orthopaedic shoulder outpatient clinic, consecutively, all new patients above age 18 are informed about the study by telephone. Patients who have difficulty understanding the explanation, because of language deficiency are excluded. The patient routine contains three measurement moments T0, T1 and T2.

During the first visit (T0), all new patients are asked whether they want to participate in the research project. If the answer is positive, the patients sign an informed consent form. Then a thorough history is taken and the patients will undergo a physical examination including the above mentioned clinical tests by the second author ([name]). Subsequently, scores on the WORC, SF-36 and the Constant Score are obtained, and patients are asked to rate their shoulder hindrance on an 11-point scale from 0 (no hindrance) to 10 points (extreme hindrance), all by the second author ([name]). (See the appendix section for details on obtaining the Constant Score.) In case of suspicion of instability or a cuff tear MRI is performed. If MRI is contraindicated and a cuff tear is suspected ultrasound is performed. Patients do not receive any therapy at T0.

The next visit is scheduled 2-3 weeks after T0. This visit is defined as T1. At T1 the WORC, SF-36 and Constant Score are scored again. In addition, the patients are asked to rate their shoulder hindrance on the 11-point scale to check whether their symptoms have changed since their last visit.

At T1 either conservative treatment is started or the indication for surgery is made.

In Group 1 an arthroscopic rotator cuff repair is performed. In case of an irreparable cuff tear due to size, atrophy or fatty degeneration the patient is excluded from the study.

In Group 2 conservative treatment is started by injection, physiotherapy and activity adjustment. Surgery is performed when conservative treatment failed. Arthroscopic subacromial decompression is in those cases performed and in patients with calcific tendonitis the calcium deposit is removed. If during arthroscopy an asymptomatic cuff tear is found it is repaired, but these patients are then excluded from the study.

In Group 3 patients receive conservative treatment or surgery when indicated. A labral or capsular repair is performed as needed.

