Patients eligible for assignment to more than one group (e.g., those with both instability and impingement) are excluded from our study, because specificity of the WORC between the groups cannot be measured.

Patients with additional shoulder pathology like adhesive capsulitis, AC-pathology and osteoarthritis are excluded and patients with previous surgery are excluded as well.

At T2, either six weeks after starting conservative therapy or three months after operative therapy, the WORC, SF-36 and Constant Score are obtained again.

Patient characteristics like age, sex, hand dominance and Workers' Compensation claim are recorded and taken into account during data analyses, because we are comparing groups. If power permits we will control these group-characteristics.

Data will be analyzed with SPSS 15. Retrieved data from T0 and T1 will be checked for completeness and entered into Excel.

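### The absolute 'high' or 'low' verdict on WORC responsiveness depends on how many patients benefit, because no patient-level indicator of change is used at T2

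*Protocol article*

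**What the plan says.** The Responsiveness section gives the definition and the method in one sentence: "Responsiveness, or the ability of an instrument to detect clinically important change, will be determined by calculating the standardized response means and effect sizes". These are calculated from T0 and T2 for WORC, SF-36 and Constant Score within each subgroup. The SRM is "mean change in score from T0 to follow-up (T2)/standard deviation of change in score"; the ES is "mean change in score from T0 to follow-up (T2)/standard deviation of T0 score". Their size "will be interpreted using the Cohen standard of greater than 0.20 for small effects", with 0.50 for moderate and 0.80 for large. No restriction or split by whether the patient changed is stated, and no correlation between change scores.

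The hypotheses in the Background are high responsiveness in groups 1 and 2, and low responsiveness in group 3 for physical symptoms and social function.

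Under Patient routine, the 11-point hindrance rating is taken at T0. At T1 "the patients are asked to rate their shoulder hindrance on the 11-point scale to check whether their symptoms have changed since their last visit". The Reliability section describes its use at those two visits only. At T2 "the WORC, SF-36 and Constant Score are obtained again"; hindrance is not on that list.

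The Background also records that the original evaluative test of the WORC used patients "who reported that their symptoms had changed".

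**The concern.** The definition concerns detection of clinically important change. The statistic is a group mean change divided by an SD. That mean is the product of two things: how much the patients truly changed, and how well the score registers it. Without an independent sign of which patients changed, the two cannot be separated.

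The absolute verdict can then err in either direction. A good instrument may look only moderately responsive where few patients benefit. A score that drifts by the same amount in everyone may look highly responsive while saying nothing about who improved. The predicted low responsiveness in group 3 has the same ambiguity.

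Responsiveness is one of the three properties named in the aim. The plan already has a patient-rated item for noticing change, but schedules it only across the interval in which no change is expected.

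**Working it through.** The protocol states no target value or sample size for responsiveness, so there is no figure of its own to reproduce. The check asks how the SRM behaves when the instrument is held fixed and only the share of patients who benefit varies.

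**Inputs**
- Definitions of SRM and ES and the 0.20/0.50/0.80 cut-offs: Responsiveness section.
- Retest ICC 0.90: an assumption, set at the threshold hypothesised in the Background (ICC above 0.9). The value 0.95, the retest coefficient named under Patient assignment, is used as a second case.
- True improvement of 0.8 baseline SD in improvers and none in the others: an assumption without a source in the documents.
- Share improved, 50% or 90%: also assumed. The Background cites more than 90% good to excellent results after arthroscopic repair, and Table 1 runs from 44% (open repair of massive tears) to 95%. These are end-state ratings and not shares improved, and none concerns groups 2 or 3.

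**Formula** (in units of baseline SD, p = share improved, d = 0.8)
- Mean change = p × d, which is also the ES.
- Variance of change = 2(1 − ICC) + p(1 − p)d².
- SRM = mean change / √(variance of change).

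**Same instrument, ICC 0.90**
- p = 0.5: 0.40 / √(0.20 + 0.16) = 0.40 / 0.60 = 0.67 (moderate).
- p = 0.9: 0.72 / √(0.20 + 0.0576) = 0.72 / 0.508 = 1.42 (large).
- Improvers alone, at any p: 0.80 / √0.20 = 1.79.

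**Same instrument, ICC 0.95**
- p = 0.5: 0.40 / √(0.10 + 0.16) = 0.78.
- p = 0.9: 0.72 / √(0.10 + 0.0576) = 1.81.

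The ES in this set-up should not be used as evidence. With d fixed at 0.8 it equals 0.80 even if everyone improves, so it can never exceed 0.80 at any response rate.

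**Uniform shift of 0.4 SD unrelated to individual change, ICC 0.90**
- SRM = 0.40 / √0.20 = 0.89 (large); ES = 0.40 (small). The two statistics disagree here, so this example misleads through the SRM only. Splitting by patient-rated improvement would expose it: the SRM would be 0.89 in both subsets.

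**A second set of assumptions** (T0 SD 20 points, reliability 0.90, improvers gain 25 points with SD 8, others 0)
- Error variance of change = 2 × 400 × 0.10 = 80.
- 10% improved: 2.5 / √(80 + 6.4 + 56.25) = 0.21.
- 90% improved: 22.5 / √(80 + 57.6 + 56.25) = 1.62.

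The band again moves from small to large with the instrument unchanged.

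**Precision of the remedy**
- For an anchor correlation of 0.5 at n = 30, Fisher's z gives 0.549 ± 1.96/√27, so a 95% CI of about 0.17 to 0.73.
- For an SRM of 0.80 the approximate SE is √(1/n + SRM²/(2n)). At n = 30 the 95% CI is about 0.39 to 1.21. In a half-group of 15 the SE is √(0.0667 + 0.0213) = 0.30, so about 0.22 to 1.38.

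**The case against.** **Comparators.** SRM and ES are also computed for SF-36 and Constant Score in the same patients, at the same visits and under the same therapy. If few benefit, all three fall together, so the standing of the WORC relative to the others is largely protected. This stands, and it limits the point to the absolute reading. The protocol states no criterion for the relative comparison, however, and its hypotheses are worded in absolute terms.

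**Known groups.** A score that shifts equally in every group would contradict the prediction for group 3. That is a partial safeguard. It does not help within groups 1 and 2, and the Discussion itself concedes that the groups differ in treatment modality and that T2 timing depends on therapy.

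**The SF-36 and MCID sentence.** It stands under Responsiveness and could be meant as a link to clinical change. Its wording is open, but it follows a sentence on differences between groups and names no patient-rated anchor.

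**Condensed article.** Correlations with SF-36 and Constant Score change need no new data and could be specified in an analysis plan that is not shown. That is fair. A hindrance rating not collected at T2, by contrast, cannot be recovered later.

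**A stronger reading** would be that the verdict reflects only how well therapy worked, and that the study dropped a safeguard. The documents do not support it. The hindrance item was introduced to check stability for the retest and was never planned as a responsiveness anchor. The condition that patients had reported change belongs to another study's sample and was never adopted here. The protocol also does not equate high responsiveness with a value above 0.80.

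**Conclusion.** The point holds for the absolute Cohen-band verdict within each group. That verdict does not test the protocol's own definition of responsiveness, because it varies with the share of patients who benefit: under the stated assumptions the SRM for one instrument goes from 0.67 to 1.42 as that share goes from 50% to 90%. The direction of the effect follows from the formulas; its size rests on assumed values for reliability, improvement and response that the documents do not supply. If nearly all patients improve markedly, the planned statistics will come out large and the practical loss in groups 1 and 2 is smaller.

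The comparison across the three instruments is less affected and remains useful. SRM and ES are legitimate descriptive statistics; the weakness lies in resting the conclusion on their absolute size alone. This is an inexpensive improvement and not a flaw that invalidates the study.

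**What to change.** 1. Under Patient routine, add the 11-point hindrance rating to the T2 measurements.
2. Under Responsiveness, add correlations of T0-T2 change in WORC with change in hindrance, Constant Score and SF-36 in each group, with expected directions stated in advance. On the raw WORC scale (high = worse), these are positive with hindrance and negative with the other two. They reverse if the percentage-of-normal format in the Appendix is used, so the format should be named.
3. Report SRM and ES separately for patients improved and not improved by their own rating, with a cut-off that the investigators justify in advance. The documents give no basis for a particular value.
4. Base the responsiveness conclusion on items 2 and 3 together with the SRM/ES comparison across the three instruments. Keep the all-patient Cohen bands as description.

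Items 2 and 3 belong together. The correlation also depends on how varied the changes are: in the 90% example, the correlation of observed with true change is √(0.0576/0.2576) = 0.47 for a sound instrument.

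The cost is one question at an existing visit and a few analyses. The downside is imprecision, since the improved and unimproved subsets will each be below 30. Results should be reported with confidence intervals and read accordingly.

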• will be more specific to determine the extent of complaints and change in time supposed to be caused by therapy in patients in the groups 1 and 2 when compared to patients in group 3.

It is the experience of orthopaedic surgeons, also mentioned in textbooks[24,25] that patients with a rotator cuff tear (group 1) suffer pain and weakness when they use the ruptured part of the rotator cuff. In patients with DRC (group 2) patients show tendonitis resembling, more continuous, pain. For instance in this group, inability to raise the arm is rather caused by pain than by lack of strength. Patients with instability (group 3) in general complain about dislocations, subluxations or a sense of instability[26,27]. For this group of patients it is easier to avoid provocative movements compared to patients with rotator cuff disease.

The WORC consists of 5 domains: (1) physical symptoms, (2) sports and recreation, (3) work, (4) social function, and (5) emotions. We expect that the scores for each domain will not differ significantly from each other in group 1 and 2, because Kirkley stated that the frequency importance products of the 21 items have a narrow range[15]. On the contrary, based on our experience as orthopaedic surgeons, we assume that especially the domains physical symptoms (1) and social function (4) in group 3 will be rated better, because in the first domain many items involve pain and in the 4^th ^domain the provocative actions would be avoided easier by patients with instability. Resulting from these expectations, we assume that the responsiveness in group 3 will be low for domain 1 and 4.

Unique in our study design is that the patient selection and assignment into subgroups is performed in a continuing clinical process, including both interventions at the outpatients' department and surgical interventions. In this dynamic clinical setting patients can be transferred between the subgroups and inclusion can be performed continuously.

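### Responsiveness is computed from T0 although treatment starts no earlier than T1, so any mean change in the untreated 2-3 weeks between them counts as response

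*Protocol article*

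**What the plan says.** The Responsiveness section gives both indices the same numerator, the "mean change in score from T0 to follow-up (T2"). It defines the SRM as "mean change in score from T0 to follow-up (T2)/standard deviation of change in score" and the effect size as "mean change in score from T0 to follow-up (T2)/standard deviation of T0 score", for WORC, SF-36 and Constant Score in each subgroup. Both are read against the Cohen cut-offs 0.20, 0.50 and 0.80. The Discussion repeats the baseline: "Responsiveness is tested by comparing T2 and T0".

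The Patient routine section sets the timing. "Patients do not receive any therapy at T0". "The next visit is scheduled 2-3 weeks after T0", and all three instruments are scored again at that visit. "At T1 either conservative treatment is started or the indication for surgery is made". T2 falls six weeks after the start of conservative therapy or three months after surgery.

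The Reliability and Validity sections use the T1 scores. The Reliability section expects stable symptoms between T0 and T1 and takes a hindrance rating at both visits to detect change. It states no consequence for responsiveness if change is found. The article gives no reason for choosing T0 over T1 as the responsiveness baseline.

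**The concern.** The T0-T2 difference contains an interval that is untreated by design. For conservatively treated patients that is 2 of 8 weeks (25%) to 3 of 9 weeks (33%) of the whole window. Any mean change in it, whether from natural course, regression to the mean after referral or measurement conditions, goes into the numerator of both indices.

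Measurement conditions also differ between the two visits. At T0 the scores follow a physical examination with the listed clinical tests. These include resistance and provocation manoeuvres and a test with a subacromial lidocaine injection, whose positive result is reduced pain. No such examination is described at T1. The direction of any effect, and the number of patients given the injection, are not stated.

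At stake is the label (small, moderate or large) attached to each instrument in each group. If drift differs between groups, the contrast of groups 1 and 2 with group 3 is affected too.

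**Working it through.** **Inputs from the protocol article:** baseline T0; no therapy before T1; T1 at 2-3 weeks with all three instruments rescored; cut-offs 0.20, 0.50 and 0.80; no T0-T1 change expected. The article states no expected SRM, effect size, SD or drift, so there is no figure of its own to reproduce. All sizes below are assumptions.

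**Step 1, general form.** Let *d* be the mean untreated change T0 to T1 and *e* the mean change T1 to T2, both in baseline SDs and counted positive for improvement. Assume equal SDs and pre-post correlation *r*.

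- Effect size: *e + d* from T0; *e* from T1.
- SRM: (*e + d*)/√(2 − 2*r*) from T0; *e*/√(2 − 2*r*) from T1.

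Drift thus adds exactly *d* to the effect size and *d*/√(2 − 2*r*) to the SRM. Deterioration before T1 would lower both. With *d* = 0 the baselines agree.

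At *r* = 0.5 the divisor is 1. With *e* = 0.5, drift of 0, 0.1, 0.2 or 0.3 gives 0.50, 0.60, 0.70 or 0.80 from T0, against 0.50 from T1. With *e* = 0 and *d* = 0.3, T0 gives 0.30 (above the cut-off for small) and T1 gives 0. For *r* from 0.4 to 0.7, *d* = 0.3 adds 0.27 (0.3/√1.2) to 0.39 (0.3/√0.6) to the SRM.

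**Step 2, in points.** Assume a 0-100 scale and SD of change 15, so SRM = (response + drift)/15.

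| Drift (points) | Added to SRM | Response 10 | Response 8 |
|---|---|---|---|
| 0 | 0 | 0.67 | 0.53 |
| 1.5 | 0.10 | 0.77 | 0.63 |
| 3 | 0.20 | 0.87 | 0.73 |

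The 0.80 cut-off corresponds to 0.80 × 15 = 12 points. A 10-point response crosses it once drift exceeds 2 points; an 8-point response needs more than 4 and stays moderate throughout the table.

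**Step 3, would the reliability analysis expose the drift?** Assume SD 20 and an ICC of 0.93 without drift: between-patient variance 0.93 × 400 = 372. A 3-point mean shift between two sessions adds 3²/2 = 4.5 to the total variance. The agreement ICC becomes 372/404.5 = 0.92, still above the hypothesised 0.9. A satisfactory ICC is therefore compatible with a drift that adds 0.20 to the SRM.

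**Step 4, averaging T0 and T1.** With error variance Vₑ and true-change variance Vₜ, the SD of change is √(Vₜ + 2Vₑ) with one baseline score and √(Vₜ + 1.5Vₑ) with the mean of two. Assume baseline SD 20 and reliability 0.90, so Vₑ = 40.

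- SD of true change 12: √(224/204) = 1.05.
- SD of true change 15: √(305/285) = 1.03.

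The SRM rises by about 3-5%. The averaged baseline, (T0 + T1)/2, leaves half of any drift in the numerator, whereas T1 alone leaves none of it.

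**The case against.** Several points for the plan stand.

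- **T0 is a legitimate baseline.** Both T0 and T1 precede therapy, and T0 is used consistently in the Responsiveness section and the Discussion. A reader might infer that T0 is not a pre-treatment score or that the article contradicts itself; neither is so.
- **T1 is not wasted.** A reader might infer that the T1 scores go unused. They supply the retest for reliability and a second time point for validity; only responsiveness leaves them out.
- **The harm is conditional.** The protocol expects no symptom change between T0 and T1, and no drift is documented. A reader might infer that the responsiveness figures will be biased; the documents support only that they would be if mean scores moved.
- **The link to therapy is looser than it looks.** The phrase "change in time supposed to be caused by therapy" belongs to the hypothesis on specificity between groups. The responsiveness hypothesis asks only for high responsiveness in groups 1 and 2, and the Responsiveness section speaks of detecting clinically important change. Real improvement before T1 is something a responsive instrument should register.
- **Shared drift matters less for ranking.** All three instruments use the same baseline, so a drift equal in SD units shifts absolute size more than order. Equality is not assured, however, for a physician-administered score with strength testing, a disease-specific questionnaire and a general one.

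The objection that drift would show up anyway is only partly right. The hindrance rating and the T0-T1 comparison could reveal it, but step 3 shows the ICC need not, and nothing says what would follow for responsiveness.

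**Conclusion.** The point holds in a limited form. Both indices run from T0, treatment begins no earlier than T1, and a later pre-treatment score on every instrument is scheduled but not used for responsiveness. Any mean T0-T1 change therefore enters the effect size one-for-one and, with an assumed SD of change of 15, adds 0 to 0.20 to the SRM for drift of 0 to 3 points. That can move a result from moderate to large but need not. The actual drift cannot be derived from the documents and may be nil.

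A reader might also infer that T1 is the true pre-treatment score for everyone. For conservative treatment it is. For surgery only the indication is made at T1, so a wait of unstated length follows, and in group 2 surgery comes after failed conservative treatment. T1 reduces non-treatment change but does not remove all of it. Nor does the 3-5% gain in SRM apply to T1 alone; it comes only from averaging T0 and T1.

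This is a cheap improvement of minor to moderate weight.

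**What to change.** Compute the SRM and effect size from T1 to T2 for WORC, SF-36 and Constant Score alike, with the SD of the T1 score as the effect-size denominator. Alternatively, use the mean of T0 and T1 as baseline for all patients; this gains a little precision but only halves any drift. Fix one of the two in advance.

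Report the T0-T2 figures as a sensitivity analysis, show the mean T0-T1 change per instrument and group, and state how patients whose hindrance rating changed before T1 are handled for responsiveness. Note in the report that, for surgical patients, T1 is not the immediate pre-operative score.

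The cost is a change of formula, since all the data are already scheduled. The small downside is that patients without a T1 score drop out of the analysis or need T0 as a fallback, which mixes two baseline definitions. If a fallback is used, give the number of such patients. If the no-drift expectation holds, the expected result is unchanged.
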